## Methods and design

### Participants

This study will include young children with ASD and their parents who will be recruited through state child development centres, diagnosticians, private service providers, parents’ support groups, community forums, local print media advertorials and public advertisements.

The eligibility criteria for the trial will include:

### Inclusion criteria

*Children aged less than 4;3 months (51 months)*: At the time of screening for eligibility, potential participants’ age would be less than 4 years and 3 months. In Australia, the average age of a child with ASD at the time of formal diagnosis is 49 months [13]. The early key developmental areas that are primarily targeted by the TOBY intervention used in this trial calls for the inclusion of young children and their primary caregivers as necessary participants for this study.
*Diagnosis of autism spectrum disorder:* Participants will be children who receive a clinical diagnosis of ASD according to DSM-IV-TR or DSM-V guidelines [56, 57] within the 12 months prior to the time of screening for eligibility. This post diagnostic time is a critical period for families affected by ASD where acceptance and management of the new developmental diagnosis is coupled with many decision making processes including which of a variety of disability agencies to access in a bid to seek funding, support and gauge treatment options. Families are typically wait listed for early intervention therapies that are supported by state jurisdictions, the Commonwealth of Australia or private therapy providers. The wait list period for ASD specific treatment services can vary greatly between states and regions for both, state or privately funded operators. For this trial, participants’ clinical diagnosis of ASD will be validated as part of baseline battery of assessments and will include children who also meet the diagnostic criteria for autism or autism spectrum on the Autism Diagnostic Observation Schedule – Generic (ADOS-G) [58] or the ADOS-2 algorithm [59] for DSM-IV/ICD-10 or DSM-V/ICD-11 [56, 57].

### Exclusion criteria

*Previous use of the TOBY Playpad App.* Past exposure to the TOBY Playpad App will lead to contamination of the intervention and may contribute to a plausible spurious intervention effect.
*Significant medical or sensory/motor impairments* such as a blindness or deafness which may incapacitate and thus impede the child’s ability to use a touchscreen device like the iPad®. This will also include unstable seizure disorder.
*A traumatic head injury; genetic/neurological condition or disease* such as a diagnosis of Rett’s Disorder, Childhood Disintegrative Disorder or other neuro-developmental disorder of known aetiology such as Fragile X.

### Site recruitment

The TOBY Playpad trial will be conducted across two Australian sites: in Victoria (Monash, La Trobe and Deakin Universities) and in Western Australia (WA) at the Telethon Kids Institute. These sites have been selected based on the expertise of the multi-disciplinary research teams, the likelihood of meeting recruitment goals and the execution of the trial’s protocol as well as state specific funding. The primary coordinating site for this trial will be in WA whilst Victoria will be a satellite site with the main coordination occurring in Victoria at Monash University. Assistance with family recruitment and child assessments will be provided by La Trobe University whist technical support for the TOBY Playpad App across both sites will be provided by the computer science team at Deakin University.

### Study design

The TOBY Playpad study is a multisite, single (assessor) blind, randomised controlled pragmatic intervention trial with a parallel group design. Treatment in the form of early intervention delivered through an electronic platform like the iPad® using an application called the TOBY Playpad App in addition to ‘therapy as usual’ (TOBY therapy + therapy as usual) will constitute the treatment group. The ‘control’ group will receive any form of early intervention ‘therapy as usual’ accessed by the family through local service providers. Both groups will be assessed at baseline (Time 0) with two subsequent follow-ups at 3-(Time 1) and 6-months (Time 2) after the completion of baseline direct assessments including a battery of parent completed questionnaires. Figure 1 outlines the CONSORT flow diagram of this study.

**Fig. 1 Fig1:**
[figure not shown]
The CONSORT flow diagram for the TOBY Playpad trial

## Trial status

This is an ‘ongoing’ study. The data collection has been completed and it is being prepared for analyses.

## Procedures

### Screening and enrolment

Referred families of recently diagnosed young children with ASD will be asked to contact the site specific clinical trial coordinator to obtain parent information form about the trial. Potential participants will be invited to engage in a brief (10 min) telephone screening interview which will be based on the eligibility criteria. This contact will provide potential families with the opportunity to ask questions about the trial. Upon meeting the eligibility criteria, parents and their child with ASD will be invited to enter the trial and undergo baseline testing (2–3 h) at respective trial sites. Written informed consent from parents of eligible children will be sought prior to baseline assessments.

### Baseline assessments, primary and secondary measures

A combination of direct observation and play-based assessments administered by a research -accredited ADOS assessor will be conducted on children with ASD. This will include parent self-reports on a range of child-related and ASD specific symptoms and behaviours. In addition, questionnaires about parental competencies, stress levels and services support will also be administered. The measures will be taken at trial time points outlined in Table 1.

**Table 1 Tab1:** TOBY Playpad Trial measures

Measure	Time points T0, T1, T2^a^ unless otherwise noted	Description
Primary Measure Autism Treatment Evaluation Checklist (ATEC) [64]		The ATEC is a parent rated measure consisting of four subtest scales: Scale I. Speech/Language/Communication (14 items—with scores ranging from 0 to 28); Scale II. Sociability (20 items— with scores ranging from 0 to 40); Scale III. Sensory/Cognitive Awareness (18 items— with scores ranging from 0 to 36), and Scale IV. Health/Physical Behaviour (25 items-with scores ranging from 0 to 75). The four subscale scores can be used to calculate a total score (with total scores ranging from 0 to 180). The higher the subscale and total score, the more impaired the participant. The lower the subscale and total score, the less impaired the participant.
Secondary Measures Autism Diagnostic Observation Schedule-Generic (ADOS-G) [58]	T0, T3	The ADOS-G is a semi-structured standardised observational assessment that uses questions and activities to elicit the communicative, social, and repetitive behaviours relevant to ASD diagnosis. There are four modules which are age and language dependent. Therefore, this trial will use Module 1 (for pre-verbal children or those using single words/simple phrases (10 activities with 29 accompanying ratings) and Module 2 (children with flexible phrase speech (14 activities with 28 accompanying ratings). A standardised severity score is generated for respective modules. The lower the severity score, the less impaired the participant.
Mullen Scales of Early Learning (MSEL) [61]		The MSEL is a standardised developmental test for children (from birth to 68 months) which includes interactive tasks completed by the child to measure cognitive ability and motor development. The MSEL includes 124 items that measure five specific domains: 1) Gross Motor; 2) Fine Motor; 3) Visual Reception; 4) Expressive Language; and 5) Receptive Language. Four cognitive scales (Visual Reception, Fine Motor, Receptive Language, and Expressive Language) sum to represent an Early Learning Composite Score which measures overall cognitive functioning. A T-score, percentile, and age equivalent score can also be generated for each scale.
Symbolic Play Test (SPT) [66]		The SPT is a non-verbal standardised assessment of young children’s early concept formation and symbolisation. The SPT consists of four independent situations where the child is presented with sets of realistic representational toys and their spontaneous play is observed and recorded on a standardised checklist. The test is scored on the number of meaningful responses and connections made by the child when the objects are presented.
MacArthur-Bates Communicative Development Inventories (MCDI) [67]		The MCDI are parent report scales used to evaluate early language competence. There are two versions of the MCDI; 1) Words and Gestures (MCDI-WG) and 2) Words and Sentences (MCDI-WS). The MCDI-WG form is for 8–18 months old children while the MCDI-WS is for 16–30 months old toddlers. In both forms, parents report their child’s language development (i.e., vocabulary syntax). The MCDI were adapted for the Australian context with permission of the publishers, Paul H Brookes Publishing Co, (http://www.brookespublishing.com/customer-service/rights-permissions/)
Measure	Time points T0, T1, T2^a^ unless otherwise noted	Description
Communication and Symbolic Behaviour Scales - Developmental Profile (CSBS-DP) [68]		The CSBS-DP is a standardized assessment that measures communication and symbolic abilities as reported by a parent. The scale consists of a 24-item Infant-Toddler Checklist and assesses parents’ perceptions of their child’s communication and symbolic behaviour. The CSBS DP measures seven language predictors: Emotion and Eye Gaze, Communication, Gestures, Sounds, Words, Understanding, and Object Use. These predictors are summed to yield three Composite scores (Communication, Expressive Speech, and Symbolic). The composite scores are summed to yield a Total score.
Repetitive Behaviour Scale (RBS) [69]		The RBS is a parent questionnaire that characterizes the severity of repetitive behaviour. The RBS consists of 6 sub-domain scores: Stereotyped Behaviour (6 items - with scores ranging from 0 to 18), Self-injurious Behaviour (8 items - with scores ranging from 0 to 24), Compulsive Behaviour (8 items - with scores ranging from 0 to 24), Ritualistic Behaviour (6 items - with scores ranging from 0 to 18), Sameness Behaviour (11 items - with scores ranging from 0 to 33), and Restricted Behaviour (4 items - with scores ranging from 0 to 12). The six sub domains can be summed to yield a total score (total scores ranging from 0–129). Each item is rated on a four-point scale ranging from 0 (behaviour does not occur) to 3 (behaviour occurs and is a severe problem).
Family Empowerment Scale (FES) [70]		The FES is a 34-item rating scale assessing a family’s empowerment status, which is measured across two dimensions. The dimensions include the level of empowerment (family, service system, and community/political) and the ways empowerment is expressed (attitudes, knowledge, and behaviours). Each item is rated from on a 5-point Likert scale from 1 (not true at all) to 5 (very true). For example, parents will rate the following item: “I help other families get the services they need”.
Parenting Stress Index - Short Form (PSI-SF) [71]		The PSI-SF is a 36-item rating scale measuring the overall stress within the parent–child system. The PSI consists of three subscales: Parental Distress, Parent–child Dysfunction Interaction, and Difficult Child. Each subscale consists of 12 items rated from 1 (strongly agree) to 5 (strongly disagree), with subscale scores ranging from 12 to 60. The three domains combined form a Total Stress score (with a total score ranges from 36 to 180). A high score on the subscales and total stress score indicates increased levels of stress.
Parenting Sense of Competence Scale (PSCS) [72]		The PSCS is a 17-item scale that measures two dimensions of parenting self-esteem: Efficacy (scores range from 7 to 42) and Satisfaction (scores range from 9 to 54). A sample item includes “Being a good mother is a reward in itself”. Each item is rated on a 6-point scale from 1 (strongly agree) to 6 (strongly disagree). The total score of the 17-items represent parental confidence, with a higher score indicating a higher parenting sense of competency.
Measure	Time points T0, T1, T2^a^ unless otherwise noted	Description
Vineland Adaptive Behaviour Scale - Parent Version (VABS) [73]		The VABS is a standardized norm-referenced assessment tool used to measure adaptive behaviour. The Parent/Caregiver form includes 376-items. The VABS consists of five domains (each with 2–3 sub domains): Communication, Daily Living Skills, Socialization, Motor Skills, and Maladaptive Behaviour. An adaptive behaviour composite can also be calculated (with scores ranging from 20 to 160). Percentile ranks, adaptive levels, stanines, age equivalents, V-scale score, and standard scores can also be calculated from the raw scores
Behaviour Flexibility Rating Scale (BFRS) [74]		The BFRS is a 16-item scale assessing the behavioural flexibility in individuals with developmental disabilities. The BFRS consists of three subscales: Position/Location, Interruption/Disruption, and Interpersonal Mishaps. Using a 4-point scale, ranging from 0 (not a problem at all) to 3 (the situation causes severe problems); parents rate the severity of situations that can could be problematic to the individual. Higher total and subscale scores indicate greater behavioural inflexibility.
TOBY Playpad Intake Questionnaire	T0	The TOBY intake questionnaire consists of seven sections and is tailored to obtain parental report on children’s listening, communication, language and play skills. Items about children’s electronic media use and parents’ self-efficacy and confidence in assisting children to communicate are featured.
TOBY Playpad Follow-up & Satisfaction Questionnaire	T1, T2	The TOBY Playpad follow-up questionnaire version is as above. In addition, it contains 10 items and asks the treatment group parents (only) about the TOBY-App experience and satisfaction.
Case History Questionnaire (CHQ)	T0	The CHQ consists of eight sections and is tailored to gather socio-demographics of participants; birth; medical and developmental history of children with ASD. In addition, thinking styles of both biological parents in the form of Autism Quotient is asked.
TOBY therapy and therapy as usual Diary	T1, T2	Over 24 weeks of the intervention, both, intervention and control group parents report their children’s ‘therapy as usual’. In addition, the treatment group parents report TOBY App use termed as TOBY therapy. Both groups record relevant information at the end of each day in a diary format as featured in Fig. 3. Two diaries are provided to participants; 1) week 1–12 and 2) week 13–24.

^a^Data collection at T0 = baseline; T1 = follow-up 3 months; T2= follow-up 6 months

### Randomisation and blinding

Participants will be randomly assigned to either the ‘treatment’ or ‘control’ group based on stratification across three strata. The first stratum will be based on the trial sites (Telethon Kids Institute or Victoria). The second stratum will be Socio-Economic Status (SES) where SEIFA (Socio-Economic Indexes For Areas) for WA and Victoria [60] based on residential postcode will be used as a proxy for dichotomisation into two groups such as SEIFA decile 1 and 2 = Low SES and for decile 3–10 = High SES. The third stratum will be based on the developmental quotient (DQ) generated from the early learning composite score (cut point ≤ 50 DQ) on the Mullen Scale of Early Learning (MSEL) assessed as part of the baseline direct assessment battery [61]. A permuted block approach with a total of 8 strata (4 per site) will be used with random treatment allocation within each block of 20 randomisation sequences [62, 63]. The randomisation schedule will be generated by a computer and managed by clinical trial coordinator at the primary coordinating site in WA (JG). Clinical assessors and other investigators will be blind to the method of randomisation and treatment allocation. Given the nature of the treatment intervention, participating families are unable to be masked regarding treatment allocation. Each trial site coordinator will advise families of randomisation by telephone and a mailed letter.

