### Sample size and analyses

The analyses for this trial will be performed on an intention-to-treat basis including all participants with outcomes data available. The primary outcome - a total score on the Autism Treatment Evaluation Checklist (ATEC) [64] (range 0–180) at Time Points 1, 2 and 3 will be analysed using a repeated measures ANOVA or via a General Linear Model (GLM). Based on the study investigator’s (AW and DC) clinical judgment in managing children with ASD, a score of 72 (50th centile) and a difference of 1SD = 32 (30th-70th centile) on the ATEC can represent clinically important improvement in ASD symptoms. The aim of this intervention is to look for a small-to-moderate effect size of 0.2–0.5 with 80 % power and two-sided alpha of 0.05. This will require a sample of approximately 64 participants per treatment group. Allowing for a 10 % drop-out rate, 70 participants will be required per treatment group, thus, the trial aims to recruit a total of up to 140 participants.

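### Blocks of 20 in 8 strata do not fit 140 children, so stratification controls within-stratum balance only weakly, and the article does not say that the stratification factors enter the primary model

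*Protocol article*

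**What the plan says.** The Randomisation and blinding section of the Protocol article names three two-level factors:

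- Site: "The first stratum will be based on the trial sites (Telethon Kids Institute or Victoria".
- SES from the residential postcode: "SEIFA decile 1 and 2 = Low SES and for decile 3–10 = High SES".
- DQ from the Mullen scales: "early learning composite score (cut point ≤ 50 DQ".

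It then says "A permuted block approach with a total of 8 strata (4 per site) will be used". The only statement about block length comes in the same sentence: "random treatment allocation within each block of 20 randomisation sequences".

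Under Sample size and analyses, "This will require a sample of approximately 64 participants per treatment group". After an allowance for drop-out, "the trial aims to recruit a total of up to 140 participants". The ATEC total at three time points "will be analysed using a repeated measures ANOVA or via a General Linear Model (GLM". That section lists no model terms, so the stratification factors are neither included nor excluded. The Trial status section says that data collection is complete and that the data are being prepared for analysis.

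**The concern.** Permuted blocks guarantee equal arms only at the end of each block. If a stratum stops recruiting part-way through its first block, its arms are balanced only in part, and the longer the block, the weaker the control. Here the average stratum is smaller than one block. The SES cut makes this worse, because two deciles face eight and the low-SES strata are likely to be small.

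The analysis matters for two reasons. Where the design leaves chance imbalance in a prognostic factor such as DQ, adjustment in the model is the remaining way to correct it. Where the design does achieve balance, a model without the factors overstates the standard error. The article does not show whether the model carries them. At stake is the benefit that stratifying was meant to buy, and some precision. No excess of false positives is at stake.

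**Working it through.** **The plan's own sample size.** For d = 0.5, two-sided alpha 0.05 and 80% power, the normal formula gives 63 per arm and the t-test version 63.8, so 64. With 10% drop-out, 64/0.9 gives 72, 64 × 1.1 = 70.4, and 63/0.9 = 70. The stated 64, 70 and 140 are close enough and are not in dispute.

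**Block fit, from stated figures only.**
- Strata: 2 × 2 × 2 = 8.
- Places for one block per stratum: 8 × 20 = 160, more than 140. At least one stratum cannot fill a block, whatever the case mix.
- Mean stratum size: 140/8 = 17.5.
- At most 140/20 = 7 blocks can close in the whole trial.

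**Small strata.** If recruitment follows the deciles (an assumption), low SES is 20% of the sample: 140 × 0.2 = 28 children over four strata, 7 each. With r children in an open block of length B, the arm difference has variance r(B − r)/(B − 1). For r = 7 and B = 20 this is 7 × 13/19 = 4.79, an SD of 2.2. Simple randomisation of 7 children gives √7 = 2.6. With B = 4 the last block holds 3 children: 3 × 1/3 = 1, an SD of 1.0. In such a stratum blocks of 20 do little better than tossing a coin.

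**Simulation.** There were 20,000 trials per setting, 1:1, with 140 children spread at random over the strata. The article gives no splits, so all of them are assumed.

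| One site / low SES / DQ ≤ 50 | Strata never completing a block | Strata ending open | Children in open blocks | 95th percentile of arm difference |
|---|---|---|---|---|
| 50% / 50% / 50% | 5.6 | 7.4 | 93 | 10 |
| 50% / 20% / 50% | 4.1 | 7.9 | 62 | 12 |
| 60% / 20% / 50% | 4.5 | 7.8 | 65 | 10 |
| 70% / 20% / 40% | 5.4 | 7.8 | 68 | 10 |
| 50% / 20% / 30% | 5.5 | 7.7 | 72 | 10 |
| 70% / 10% / 30% | 5.1 | 7.5 | 49 | 10 |

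With blocks of 4, about 6 strata still end open, but they hold only about 12 children, and the 95th percentile is 4. Under simple randomisation it is 24.

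**Cost of unequal arms.** With 128 analysed and d = 0.5, power is 80.7% with equal arms and 80.4% with a difference of 12, a loss of about 0.3 points.

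**If the factors were left out of the model.** Suppose they explain a share R² of the variance of the analysed score (assumed 0.1 to 0.3).
- Comparison at one time point with full balance: the reported SE is too wide by 1/√(1 − R²), that is 1.054, 1.118 and 1.195 for R² of 0.1, 0.2 and 0.3. True size is 2{1 − Φ(1.96/√(1 − R²))}, about 3.9%, 2.8% and 1.9%.
- The same comparison simulated with blocks of 20 (126 analysed, 20% low SES, 40% with DQ ≤ 50, effect carried by DQ): size about 4.2% down to 2.6%.
- Test on change from baseline, same setting, baseline-to-6-month correlation 0.7 (assumed) and a stable DQ effect: size about 5%, power 94–95% with or without the factors. A stable effect cancels within the child, so a gain appears only if the factors predict change.

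**The case against.** Four objections deserve weight.

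1. *The article does not leave the factors out.* A reader might infer that the analysis ignores the stratification. The text does not support that: it names a model family and no terms, a GLM can carry all three factors, and covariate lists are commonly left to a statistical analysis plan, which is not at hand. This stands. The point is a request to state the terms, not a charge that they are missing.

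2. *The gain may be nil.* For a comparison at a single time point with 63 per arm and d = 0.5, adjustment would lift power from about 79.5% to 83–91% for R² of 0.1 to 0.3. A reader might carry those figures over to the planned analysis. They do not transfer to a group-by-time test, where stable factor effects cancel, and they shrink if baseline ATEC is already in the model. This stands too.

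3. *Large blocks have a merit, and the harm is small.* They make the next allocation harder to guess in a trial where families know their arm, and the scheme still balances the arms better than simple randomisation. Both are true. Neither restores balance within strata, which is what stratifying is for.

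4. *The block length is uncertain.* The wording might describe a list of 20 sequences and not a block of length 20. That is possible, and it is a reason to state the length used.

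**Conclusion.** The point holds in a limited form. If the block length is 20, it does not fit 8 strata and 140 children: that at least one stratum cannot fill a block is pure arithmetic. That about half or more of the strata never complete one (4.1 to 5.6 of 8) rests on assumed splits of site, SES and DQ. Balance within strata is weakly controlled. Overall balance is not seriously harmed.

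On the analysis, the article does not state that the factors enter the primary model. If they do not, the test is conservative for a comparison of scores (size roughly 2–4% instead of 5%) and about unaffected for change with stable factor effects. No inflated type I error and no bias follow. The precision that adjustment would recover depends on an unknown R² and cannot be fixed from the article. Nor does the text claim that the blocks balanced the strata, so there is no such claim to withdraw. With data collection complete, the model is the one part that can still be settled, and doing so is nearly free.

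**What to change.** Before analysis, state that site, SES group and DQ group, coded as used in the randomisation, enter the primary and secondary models as fixed covariates. If the treatment test is group by time, add their interactions with time. State the block length actually used, and report arm counts by stratum with the baseline data.

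The factors were needed to randomise, so no new data are required. The three main effects cost 3 degrees of freedom. Interactions over three occasions add at most 3 × 2 = 6 more, out of a planned sample of up to 140 children. The block length cannot be changed now.
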